## Sample size

Since this is a parallel-group feasibility intervention trial in a school setting, where interventions can only be done on class level (in a group) and not individually due to ethical and administrative reasons, we included 12 classes of children from the intervention school and 12 from control school. Each class has approximately 40-45 students making a total sample size of approximately 540 participants in intervention and 540 in the control arm. This sample size is sufficient to measure feasibility outcomes of 70% recruitment, retention, and treatment fidelity. As mentioned by Thabane et al., for an expected completion rate (recruitment, retention, and treatment fidelity for this study) of 75%, the minimum required sample for the pilot study would be at least 75 participants using a 95% CI for the proportion and a margin of error (ME) of 0.05, a lower bound of this CI of 0.70 [35]. Hence, the abovementioned sample size for this study is sufficient to assess the feasibility outcomes.

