**Methods:**

It is a parallel-group feasibility intervention trial. It is being conducted in two schools from lower to middle-income areas, at different locations but having the same school curriculum under the Aga Khan Education Service, Pakistan (AKESP). All children aged 9-11 years enrolled from the schools mentioned above were included. Children with any physical disability were excluded. One school received threefold intervention (focused on children, parents, and teachers) of school health education program in Pakistan (SHEPP) while the other school continued routine activity. Intervention of SHEPP is directed towards educating children, parents, and teachers about healthy behaviors. Children will receive interactive educational sessions and specially designed physical activity sessions. A 3-h health education session focusing on same healthy behaviors as for children will be conducted for both parents and teachers. Primary outcome is feasibility of SHEPP in terms of recruitment, retention, and treatment fidelity. Secondary outcomes are physical activity levels, dietary intake (of fruits, vegetable), and cardiometabolic risk factors (blood pressure, BMI, and waist circumference (WC)). The total number of children recruited were 982 (82.5 %); 505 from school A and 477 from school B and 496 (50.5) were boys.

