### Interventions

Intervention is the school health education program in Pakistan (SHEPP). SHEPP is directed towards children, parents, and teachers (Fig. 2). The basis of designing such intervention is to overcome cultural, socioeconomic barriers in performing physical activity [28]. The primary focus will be children. Intervention will be conducted within school premises over 10 months in one school while routine activities will be carried out in the control school. The 10 months cutoff has been chosen as benefits on cardiovascular risk factors are more pronounced at 10-month follow-up [29].

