## Outcome measures

### Measures of feasibility

Feasibility of SHEPP in terms of recruitment, retention, and treatment fidelity will be assessed. *Recruitment* is defined as the percentage of participants enrolled out of the total participants who were invited at baseline. *Retention* is defined as the percentage of participants who will be available for follow-up at 10 months out of those recruited at baseline. *Treatment fidelity* will be defined as the proportion of planned physical activity sessions held [33]. The trial will be considered as feasible if recruitment, retention, and treatment fidelity are > 70% recruitment [34].

Measure of potential effect

Physical activity levels (in school, out of school, moderate to vigorous physical activity, and sedentary time) assessed by change in time (minutes) spent in physical activity. Dietary patterns in terms of percentage increase in fruits and vegetable serving/day, and percentage decrease in sweetened beverages and snacks/day, cardiometabolic risk factors by change in BP, BMI, and waist circumference (WC).

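### The number of children does not determine the precision of treatment fidelity, so the 0.05 margin and 0.70 lower bound claimed for this primary criterion are not established

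*Protocol article*

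**What the plan says.** The abstract makes feasibility the primary outcome: "Primary outcome is feasibility of SHEPP in terms of recruitment, retention, and treatment fidelity". Measures of feasibility defines the three components and calls the trial feasible if they exceed 70%. Two of them are counted in children. Recruitment "is defined as the percentage of participants enrolled out of the total participants who were invited at baseline", and retention "is defined as the percentage of participants who will be available for follow-up at 10 months out of those recruited at baseline". The third is counted in sessions: fidelity "will be defined as the proportion of planned physical activity sessions held".

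The Sample size section plans 12 classes per school, "making a total sample size of approximately 540 participants in intervention and 540 in the control arm". It then states: "This sample size is sufficient to measure feasibility outcomes of 70% recruitment, retention, and treatment fidelity". The support is a single calculation with an expected rate of 75%, applied by name to all three components: "the minimum required sample for the pilot study would be at least 75 participants using a 95% CI for the proportion", with a margin of 0.05 and a lower bound of 0.70.

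On delivery, the Interventions section says: "Intervention will be conducted within school premises over 10 months in one school while routine activities will be carried out in the control school". Children's attendance at sessions is a different quantity, called adherence and described under Adherence to SHEPP.

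**The concern.** The calculation concerns a proportion of participants, and fidelity is not one. Its denominator is the number of physical activity sessions planned in one school. Enrolling 75, 540 or 1080 children leaves that denominator unchanged, and the control school, which holds no SHEPP sessions, adds nothing to it. Fidelity is named both in the sufficiency sentence and in the parenthesis attached to the expected rate, so the claim is explicit.

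What is at stake is a stated design property. The article says the design can place the lower confidence bound at 0.70 when the true rate is 75%, for each of three criteria that decide whether SHEPP is called feasible. For the criterion that speaks most directly to whether the programme can be delivered, that property has not been derived.

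**Working it through.** **Inputs from the article.** Expected rate p = 0.75, 95% confidence, margin 0.05, minimum of 75 participants, 12 classes and about 540 children per arm (Sample size). Weekly schedule: two 30-minute sessions, five daily assembly activities, and six one-minute between-class bouts on each of five days (SHEPP-physical activity sessions). Delivery lasts 10 months (Interventions).

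**Assumption.** The article does not give the number of delivery weeks. I take 30 to 43.

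**Step 1: the plan's own figure.** The required number is n = 1.96² × p(1 − p) / margin² = 3.8415 × 0.1875 / 0.0025 = 288.1, so 289. The stated 75 does not reproduce. Leaving out 1.96² gives 0.1875 / 0.0025 = 75.0 exactly, which treats 0.05 as a standard error. With n = 75 the half-width is 0.098. This is a separate error. Correcting it would give another number of participants and would still not bear on fidelity.

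**Step 2: what the children do support.** The half-width is 1.96 × √(0.1875 / n). For n = 540 it is 0.037 and for n = 1080 it is 0.026, before any allowance for clustering. These figures apply to recruitment and retention, whose denominators are children.

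**Step 3: fidelity, with sessions as n.** The same formula at p = 0.75:

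| Unit counted | Number over 30 to 43 weeks | 95% half-width |
|---|---|---|
| Twice-weekly slots, once for the school | 60 to 86 | 0.110 to 0.092 |
| Slots plus daily assembly (7 per week), independent | 210 to 301 | 0.059 to 0.049 |
| Slots, assembly and between-class bouts (37 per week), independent | 1110 to 1591 | 0.026 to 0.021 |
| Twice-weekly class-sessions, 12 classes, independent | 720 to 1032 | 0.032 to 0.026 |

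**Step 4: correlation among class-sessions.** If cancellations are shared across classes on the same day, the design effect is 1 + 11ρ. At ρ = 0.2 it is 3.2, and the class-session half-width becomes 0.057 to 0.047. At ρ = 1 it returns to 0.110 to 0.092. If the correlation is instead among sessions of the same class, the design effect is 1 + (m − 1)ρ with m = 60 to 86 sessions per class. That gives 0.063 to 0.061 at ρ = 0.05 and 0.083 to 0.081 at ρ = 0.10. The article gives no value for either correlation, so those used here are illustrative.

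**Step 5: what 0.05 requires.** By Step 1, about 289 effectively independent sessions. Whether the trial has them depends on the counting unit, the number of weeks and the correlation. The number of children enters none of these figures; the number of classes can.

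**The case against.** The best defence is that the shortfall may not exist. Delivery is by class and there are 12 classes. The section on physical activity sessions also lists assembly and between-class activity in the weekly total. Counted broadly and treated as independent, the planned sessions could give a margin well inside 0.05. This stands, and it limits the point to a margin that is not established. A reader might infer that the trial lacks adequate precision for fidelity. The article does not support that, because it settles neither the counting unit nor the correlation. The 12 tabulated sessions favour the narrow count but do not decide the matter.

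The defence can also say that the verdict on feasibility does not use the interval. Measures of feasibility compares observed rates with 70%, and Statistical analysis reports the three components as percentages. This stands too. A reader might compare the chance of passing the rule when true fidelity is 65%: about 15% with 80 slots, against 0.6% if 540 children were the denominator. That contrast is not a fair measure of harm, since the article already makes sessions the denominator and nowhere proposes to compute fidelity on children. Sessions are logged, so the proportion held in this school can be counted outright; a binomial interval treats that record as one realisation of a repeatable process. The article nevertheless claims a confidence interval property for fidelity itself.

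Reading fidelity as attendance per child does not rescue the claim, because attendance is defined separately as adherence. Nor does an unseen analysis plan: the objection is to what the Sample size section asserts, not to a missing detail.

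**Conclusion.** The point holds as a mismatch of units in a stated design property. The Sample size section claims for fidelity a precision that the number of children cannot supply, so the 0.05 margin and 0.70 lower bound are not established for this primary criterion. The true margin is undetermined. With 30 to 43 delivery weeks assumed, the main readings run from about 0.03 to about 0.11, on both sides of the claimed 0.05, and strong correlation could widen them further. The conclusion that children are the wrong unit rests on none of these assumptions; only the size of the discrepancy does. The consequence is confined to the stated precision of fidelity.

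**What to change.** In the Sample size section, limit the sufficiency sentence and the 75% / 0.05 / 0.70 calculation to recruitment and retention. For fidelity, state which activities count as planned sessions, how many are planned in the intervention school, and the 95% margin that number gives at 75%, allowing for cancellations shared across classes. If that margin exceeds 0.05, do not claim the 0.70 lower bound for fidelity.

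The cost is a reworded paragraph and one calculation based on sessions. The logbook described under Adherence to SHEPP and Methods: monitoring already records the sessions, so no further children or data are needed. The downside is that the stated precision for fidelity may become less favourable. Enrolment and the rule that compares observed percentages with 70% do not change.

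### The stated minimum of 75 participants does not follow from its own inputs (289 do); the sample still suffices for recruitment and retention, but sufficiency is not shown for treatment fidelity

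*Protocol article*

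**What the plan says.** The Sample size section takes a 75% rate for recruitment, retention and treatment fidelity alike. Citing a methods reference, it states that "the minimum required sample for the pilot study would be at least 75 participants using a 95% CI for the proportion", with "a margin of error (ME) of 0.05, a lower bound of this CI of 0.70". From this it concludes that the planned sample, "approximately 540 participants in intervention and 540 in the control arm", is enough for the feasibility outcomes. It also says that "interventions can only be done on class level (in a group) and not individually", with 12 classes of about 40 to 45 children in each school.

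Under Measures of feasibility, recruitment is a percentage of those invited and retention a percentage of those recruited. Treatment fidelity "will be defined as the proportion of planned physical activity sessions held". The trial counts as feasible if the rates are above 70%. The Recruitment section reports 1191 families invited and 982 children recruited, 505 and 477 by school.

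**The concern.** The section gives every input to a standard precision calculation, and the result printed beside them is almost four times too small. It is the only quantitative support for the primary outcomes, and the lower bound it claims equals the 70% feasibility threshold. A reader comparing 75 with about 1,080 would see a 14-fold surplus; against 289 it is 3.7-fold before clustering. A later trial that reused 75 as its minimum would miss the stated precision by a wide margin.

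The same child-based calculation is applied to fidelity, which is not measured per child. It also treats children as independent, although the section says that delivery is by class.

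**Working it through.** **Inputs.** From Sample size: p = 0.75, 95% confidence, margin 0.05, lower bound 0.70, stated minimum 75, 12 classes per school. From Recruitment: 1191 invited, 982 recruited (505 and 477). Sidedness and an ICC are not given, so both are treated as assumptions below.

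**1. Reproducing the plan's figure.** For a single proportion, n = z² p(1 − p) / margin².
- Two-sided 95%: 1.96² × 0.75 × 0.25 / 0.05² = 288.1, so 289.
- One-sided 95%: 1.645² × 0.1875 / 0.0025 = 202.9, so 203.
- Wilson or exact lower bound of 0.70 (two-sided 95%): 323 or 336.
- Finite-population correction for populations of 540 to 1191: about 188 to 232.
- Margin 0.10 instead of 0.05: 73, which contradicts both the stated margin and the stated lower bound.

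No variant with a 95% level and a margin of 0.05 gives 75. Leaving out z does: 0.1875 / 0.0025 = 75 exactly. So 75 is the number at which the standard error is 0.05, and 0.75 ± 0.05 is then roughly a 68% interval. Omission of the 1.96 multiplier is the likely source, though this is an inference.

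**2. What 75 children would give.** 1.96 × √(0.1875 / 75) = 0.098, so the lower bound is 0.652. One-sided, the margin is 0.082 and the lower bound 0.668. Both bounds are below 0.70.

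**3. What the recruited numbers give at 75%, ignoring clustering.** Half-width = 1.96 × √(0.1875 / n):
- 1191 invited: 0.025
- 982 recruited: 0.027
- 505: 0.038
- 477: 0.039

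**4. With class clustering (assumed ICC 0.02 to 0.05).** The design effect is 1 + (m − 1) × ICC, and the half-width is multiplied by its square root.

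| Children | Mean class size m | Design effect | Half-width | Lower bound at 75% |
|---|---|---|---|---|
| 982 | 982/24 = 40.9 | 1.80 to 3.00 | 0.036 to 0.047 | 0.714 to 0.703 |
| 505 | 505/12 = 42.1 | 1.82 to 3.05 | 0.051 to 0.066 | 0.699 to 0.684 |
| 477 | 477/12 = 39.8 | 1.78 to 2.94 | 0.052 to 0.067 | 0.698 to 0.683 |

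The effective number stays at or above 289 if the ICC is at most about 0.06 for all 982 children, or about 0.017 to 0.018 for one school.

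**5. Treatment fidelity.** The denominator is planned sessions, and their number is not stated. If 60 to 86 are assumed for the twice-weekly sessions over the 10 months, the half-width at 75% is 1.96 × √(0.1875 / 60) = 0.110 to 1.96 × √(0.1875 / 86) = 0.092. If sessions were instead counted separately in each of 12 classes (720 to 1,032), the same formula gives 0.032 to 0.026, before allowing for correlation between sessions of a class. The answer turns on a session count that the section does not use.

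**The case against.** The strongest reply is that the wrong figure changed no design decision. The sample came from taking 12 classes per school, and both the planned and the recruited numbers exceed 289, overall and in each school. That stands.

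A reader might infer that the trial is too small, or that a 70% lower bound fails where it matters. The article does not support this. For all 982 children the lower bound at 75% stays above 0.70 across the whole assumed ICC range. The single-school shortfall depends on an assumed ICC, and Measures of feasibility sets no criterion per school. The feasibility rule compares the rates themselves with 70%, not a confidence limit, so a somewhat wider interval cannot alter the stated verdict.

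Recruitment is also already known: 982/1191 = 82.5%, with an unclustered lower 95% limit of 0.803. Class delivery is a weak reason to expect clustering there, because consent was decided family by family and the intervention school was allocated after baseline.

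It can further be said that 75 is credited to a cited source. What that source prints cannot be checked here. The protocol nevertheless adopts the figure for its own three outcomes beside inputs that contradict it, so the attribution does not rescue it. It does mean that 289 should not simply be swapped into a sentence credited to that source.

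The fidelity point is a mismatch of units, separate from the arithmetic. It stands at any enrolment.

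**Conclusion.** The figure of 75 is wrong for its stated inputs. The two-sided requirement is 289, a factor of 3.9 (289/75), or 203 if one-sided. This needs no assumption beyond the section's own numbers and the standard large-sample formula.

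The conclusion that the sample is sufficient holds for recruitment and retention overall, with a half-width of 0.027 unclustered and 0.036 to 0.047 at an assumed ICC of 0.02 to 0.05. For one school alone the margin of 0.05 is met unclustered (0.038 to 0.039) and is exceeded at those ICCs (0.051 to 0.067). For treatment fidelity the conclusion is unsupported, because no number of children determines its precision.

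Severity is moderate: the justification needs correcting, while enrolment and the feasibility rule are unaffected.

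**What to change.** In the Sample size section:
- Recast the sentence as the authors' own calculation: 289 participants for a two-sided 95% interval with a margin of 0.05 at 75%, with the sidedness stated.
- Give the expected half-width from the recruited numbers, overall (982) and by school (505 and 477), with a class-level design effect over a stated ICC range such as 0.02 to 0.05, labelled as an assumption.
- Limit the child-based sufficiency claim to recruitment and retention.
- State how many physical activity sessions are planned and whether they are counted per school or per class, and base the precision of treatment fidelity on that number.

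The cost is wording only. No extra enrolment is needed; the one downside is a less favourable stated precision.

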## Recruitment

We aimed to recruit children from schools working under the AKESP, primarily because, all these schools have the same design of curriculum and extracurricular activities. There are 3 schools working under the AKESP and based on logistics, we decided to conduct SHEPP in 2 schools within 10-km distance from the study center. Approval was taken from the head of schools in AKESP. After these principals of both schools were approached and at least 2 detailed meetings were held to discuss the designing of the study and recruitment. List of children aged 9-11 years studying in the morning shift (in general class 2 and 3) were obtained from the principals, and 1280 students were assessed for eligibility. After this informed consent and assent forms were distributed in each class by the PI and research staff of both schools. A note was also written in their dairies so parents could understand about SHEPP. One-week time was given to parents to agree or disagree to consent. Parents were given contact numbers of PI in case they have any queries. The consent forms and assent forms were distributed to 1191 eligible parents and their children, out of which 1116 (93.7%) agreed to participate. In all, the total number of children recruited were 982 (82.5 %); 505 from school A and 477 from school B. Out of them, 496 (50.5) were boys. To improve recruitment and to maintain interest of the participants posters will be developed which will be posted in each class and in the corridors.

## Assignment of interventions

This is a non-randomized study. One school is allocated to SHEPP intervention after baseline data collection while the other school will carry on routine activity and will be subjected to intervention after follow-up data collection. The decision of selection of school for intervention therefore was based on convenience and was not randomized. The data collectors who will collect data will be blinded to the assignment of intervention. The physical activity trainer will conduct sessions in the intervention school and will have no role during the data collection.

## Data collection, management, and analysis

### Data collection

Data collection will be done by trained data collectors who will be trained by the primary investigator for (a) filling data collection forms, (b) measurement of blood pressure, waist circumference, height, and weight. Assessment of outcomes will be done at baseline and then after 10 months of intervention by the data collectors. Physical activity would be assessed using the validated youth physical activity questionnaire modified for children at baseline and follow-up [36]. Based on the findings of a previous pretesting and piloting study (unpublished), netball, rugby, skiing, snowboarding, sledging, skateboarding, and walk-the-dogs were excluded, as these are very uncommon activities and sports in our settings. However, some common traditional games such as Kabaddi (wrestling), Pahel dooj (hopscotch), Kho kho (game of chase), Pithu garam (dodge ball), kittening, bay blades, marbles, and activities related to ascending stairs were included. In addition, religious activities like performing prayer, recitation of Quran—the holy book, and household chores like sweeping, moping, cooking, dishwashing, and grocery purchase were incorporated. Finally, the modified version consists of 71 different activities in the same seven domains of the original YPAQ form. Physical activity will also be measured objectively using Mi wrist bands for at least 5% (*n* = 50) of the participants, to check the validity of physical activity measured by the questionnaire. Mi wrist band has shown 96% accuracy of measuring physical activity when compared to the gold standard [37]. Dietary assessment will be done using a 24-h dietary recall. Number of raw fruit and vegetables, number of sugar-sweetened beverages and snacks/day that are eaten will be recorded at baseline and follow-up. The dietary recalls will be conducted by trained staff on non-consecutive day. Blood pressure will be recorded using Omron m5 monitors using a pediatric cuff [38].. Weight would be recorded using Tanita’s digital weight scales. Community-setting aluminum scale was used to measure height with subjects standing barefooted (without head cover).

